## Abstract

**Background:**

Better communication among field health care teams and points of care, together with investments focused on improving teamwork, individual management, and clinical skills, are strategies for achieving better outcomes in patient-oriented care. This research aims to implement and evaluate interventions focused on improving communication and knowledge among health teams based on points of care in a regional public health outreach network, assessing the following hypotheses: 1) A better-working communication process between hospitals and primary health care providers can improve the sharing of information on patients as well as patients’ outcomes. 2) A skill-upgrading education tool offered to health providers at their work sites can improve patients’ care and outcomes.

**Methods/Design:**

A quasi-experimental study protocol with a mixed-methods approach (quantitative and qualitative) was developed to evaluate communication tools for health care professionals based in primary care units and in a general hospital in the southern region of São Paulo City, Brazil. The usefulness and implementation processes of the integration strategies will be evaluated, considering: 1) An Internet-based communication platform that facilitates continuity and integrality of care to patients, and 2) A tailored updating distance-learning course on ambulatory care sensitive conditions for clinical skills improvements.

The observational study will evaluate a non-randomized cohort of adult patients, with historical controls. Hospitalized patients diagnosed with an ambulatory care sensitive condition will be selected and followed for 1 year after hospital discharge. Data will be collected using validated questionnaires and from patients’ medical records. Health care professionals will be evaluated related to their use of education and communication tools and their demographic and psychological profiles. The primary outcome measured will be the patients’ 30-day hospital readmission rates. A sample size of 560 patients was calculated to fit a valid logistic model. In addition, qualitative approaches will be used to identify subjective perceptions of providers about the implementation process and of patients about health system use.

**Discussion:**

This research project will gather relevant information about implementation processes for education and communication tools and their impact on human resources training, rates of readmission, and patient-related outcomes.

**Electronic supplementary material:**

The online version of this article (doi:10.1186/s12913-016-1626-9) contains supplementary material, which is available to authorized users.

## Background

In structured societies, better care for all must be delivered in a timely and effective manner. Universal health systems face shortages of funding, increasing patient demand, and more complex treatment options [1]. The Brazilian Unified Health System (Sistema Único de Saúde, SUS) aims for the provision of universal access to the population, prioritization of equity in the health services, and integrality across assistance levels [2].

The Regional Healthcare Attention Network (RHAN) is the result of a public policy that has been incorporated in the SUS. RHAN is a framework recommended by the Brazilian Ministry of Health to improve the coordination among the levels of the health care system [3]. The core idea of RHAN is that better communication and the use of evidence-based information by health teams at different points of care should result in coordination and integration in terms of how patients are viewed and managed [4]. Primary care has the most relevant role in RHAN’s coordinating efforts to assess patients who should be referred to the other levels of care (e.g., specialists and hospitals), but patients receiving treatment at other hierarchical levels are also received and managed by the primary care sector [5].

Effective communication among teams based in hospitals and those based in primary care units (PCU) is an essential factor for RHAN functioning regarding patient safety and continuity of care. Hospital discharge summaries have been the main tool used to accomplish these tasks. Frequently, these discharge summaries are incomplete, lacking critical information, and of poor quality. Additionally, they sometimes fail to reach the PCU teams in a timely manner. This lack of communication and information exchange can increase the risk of hospital readmission and lead to discontinuity in patient care [6–9]. Hospitalization rates for ambulatory care sensitive conditions (ACSC) have been inversely correlated with the effectiveness of primary care attention. However, there is currently no consensus on which diseases or conditions should make up the ACSC lists, as these can vary between countries and regions. The Brazilian Ministry of Health developed an ACSC list that includes chronic and infectious diseases [10].

Another critical point for RHAN is the implementation of evidence-based recommendations into routine clinical practice, evidence that can lead to better clinical outcomes for patients [11]. Nevertheless, there is some resistance from health professionals to adhering to evidence-based protocols, because many of these protocols would not be applicable to the actual working conditions of these professionals—the so called “real world” assistance setting. A further obstacle is that many protocols contain too much information and need to be synthesized [12, 13]. Keeping health professionals updated on standards of practice based on patients’ needs is also a challenge. A recent systematic review on continuing medical education in the United States concluded that keeping informed of developments in their field, improves physicians’ performance and patients’ health outcomes, with the positive effect on physicians’ performance being more reliable [14]. Despite the positive impact of continuing medical education, the extent of this effect is unknown, underscoring the need for a debate on effective strategies to keep health professionals updated [15]. The desired health professional profile for the 21st century will synthesize the available information and resources to make better patient management decisions. In pursuit of this goal, several new technologies can be applied to offer information and support, and to improve teamwork [16].

To overcome the fragmentation of health care, which creates a burden for both patients and the health system, knowledge and communication management should help to build capacity among health professionals, empowering them to move toward transformative action. This article describes the protocol for the implementation of integration strategies based on innovative approaches to improve communication and knowledge refinement among health professionals, as well as the study protocol for the short-term impact evaluation of this implementation effort.

## Methods/design

### Research setting

Hospital Municipal [name] (HMMD) is a large municipal government-funded general hospital (300 beds) located in the south of São Paulo City (M’Boi Mirim District). The hospital is managed by Hospital Israelita Albert Einstein (HIAE) under a public–private partnership. It is the unique referral hospital for 600,000 people who are registered in 31 PCUs covered by the primary care teams. For the planned study, the 18 PCUs managed by the Center of Studies and Research [name] (CEJAM), a non-government organization that manages the primary care under a public–private partnership framework, will be selected as a convenience sample. Table 1 provides an overview of the study objectives and their associated methods.

**Table 1 Tab1:** Overview of study methods by objective

Element	Objective 1	Objective 2	Objective 3	Objective 4
Objective	To implement and evaluate an Internet-based platform that links health providers at a public hospital to18 primary care units (PCU) to improve communication among health services	To promote and evaluate a distance-learning course (DLC) to update health professionals on the clinical management of ambulatory care sensitive conditions (ACSC)	To verify the impact of the two strategies (communication and course) on patients’ hospital outcomes (30-day readmission rateslength of stay and mortality)	To verify the long-term impact of the two strategies (communication and course) through the follow-up of the patient cohort
Design	Longitudinal study of communications among health services	Cross-sectional study of the course evaluation and longitudinal study of enrolled health care providers	Longitudinal study of patients with ACSC using hospital electronic medical records	Longitudinal cohort study
Procedures	1. Platform development 2. Registration and training of professionals 3. Use the platform in the following ways: i. The hospital sends an admission warning and a structured questionnaire on patient’s information to the PCU ii. The PCU manager responds with information about the patient iii. Hospital nurses enter the information in the patient’s electronic medical record iv. The hospital sends the discharge summary to the PCU	The course consists of five modules and uses discussion forums, case studies, web conferences, and face-to-face meetings Information is obtained from the students and the DLC platform	This phase uses patient data collected from hospital electronic medical records	Selection of eligible patients among all ACSC hospitalized patients Administration of questionnaires by the research team 1-year follow-up at the PCU or the patient’s home Gathering of information from the PCU’s paper-based medical records, covering at least 1 year before and 1 year after the hospitalization. Selection of eligible patients for telemedicine consultation Training of all interviewers, inter-rater agreement analysis
Participants/ Research units	Communications among the health providers and the research team	Health care providers who signed the informed consent form agreeing to volunteer for this research	All hospital admissions of adult patients who had at least one ACSC from 2013 to 2017	Adult patients admitted to the hospital with an ACSC who are registered at any PCU enrolled in the study and are able to respond to questionnaires and sign the informed consent form
Measures	Frequencies of alerts sent by the hospital, answers sent by the PCU, patients’ information being included in the electronic medical record, discharge summaries being sent by the hospital to the PCU Duration of time between each of these steps	DLC: Frequencies of students’ access to didactic materials, participation in forums and face-to-face meetings Professionals: sociodemographic characteristics, quality of life, mindfulness, clinical types of burnout, and primary care attention attributes.	Patients: Main and secondary diagnoses, address, length of stay, discharge type, readmissions, episodes in the emergency department, reference PCU Medical record audits: Content quality of diagnosis, anamnesis, physical exam, lab exams, discharge summary, nurse registers	Patients’ information at inclusion: Sociodemographic characteristics, quality of life, primary care attention attributes. Patients’ information at follow-up: Same as in inclusion, plus PCU medical record information, geographical location of residence, consultations, medications taken, main outcomes (therapeutic plan adherence, disease complications, health services access, mortality, readmission in any hospital) Telemedicine: Reason for telemedicine request, use of diagnosis or treatment information to help with decision making, patients’ obtained outcomes PCU medical record audits: Content quality of registered information
Sample size	Not applicable	All health care providers who accept enrollment in the DLC, of eligible health care providers from the hospital and PCU health teams	All eligible patients during the study period. In total, 3422 patients with at least one ACSC were admitted from 2013 to 2014	560 patients, based on the observed incidence of 16 % readmission within 30 days, fitting a valid logistic model with up to nine covariates. Each interviewer will collect data from at least 10 patients and will be paired with another interviewer to assess inter-rater agreement
Data analysis	Absolute and relative frequencies and median and interquartile ranges with 95 % confidence intervals. Chi-square and Mann–Whitney tests to compare measures among implementation phases Social network analysis for assessing the communication structure	DLC: Absolute and relative frequencies, chi-square tests to compare measures from each module Professionals’ information: Summary measures with 95 % confidence intervals, generalized linear models to assess possible associations, generalized estimating equations to compare results over time	Patients: Summary measures with 95 % confidence intervals, generalized estimating equations for length of stay, logistic models for mortality, kernel density to assess geographical location through patients’ addresses Audits: Frequencies of adequacy of registered information with 95 % confidence intervals, chi-square tests for comparisons over time, inter-rater reliability of auditors by percent agreement and Gwet’s agreement coefficient	Baseline information: Summary measures with 95 % confidence intervals, hypothesis tests and/or generalized linear models to assess possible associations in the collected data Main outcomes (readmission rates): Summary measures with 95 % confidence intervals, generalized linear models to assess associations, generalized estimating equations to compare results over time Inter-rater agreement: Percent agreement and Gwet agreement coefficient

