### Interventions

The strategy comprises an Internet-based platform developed as a social network tailored to health professionals’ use that allows the sharing of patients’ information, documents, and treatment plans between the hospital and 18 PCUs. In addition, telemedicine support will be made available for patients who, for any reason, do not receive specialist services. An electronic knowledge platform will also be developed to keep the health professionals updated through a distance-learning course (DLC) in clinical management focused on diseases that are part of the Brazilian ACSC list.Communication platformsAn Internet-based social network that was developed using free software (based on the open source project Hubzilla [17], formerly known as Redmatrix) and was tailored for this intervention will be made available to the HMMD and PCU health teams [18]. This platform will host private communications among the health providers about their common patients. This shared information will flow through secure channels using the HTTP Secure (HTTPS) protocol to ensure that patients’ information can only be accessed by the appropriate health professionals, whose identity will be authenticated by their credentials (login and password).The platform’s interface includes a hospitalization alert that will ask for specific information that can help the hospital teams to manage the patient during their stay. The responses from the PCU will be incorporated into the hospital electronic medical record. Afterwards, the discharge summary and prescriptions will be delivered to the PCU through a similar discharge alert. Beyond the sharing of information, each alert allows for an online asynchronous conversation to develop between the professionals at each end.Additionally, a telemedicine service (already implemented at HMMD) will be made available to those patients followed during the study, who, for any reason, do not reach specialized services in the SUS. For example, long waiting times for consultations or more sophisticated exams, patient’s lack of resources to pay for transportation to the point of care, or simply absenteeism are situations that can hinder treatment plans, potentially harming patients’ clinical outcomes. Eligible patients will be referred by the primary care teams. These patients will then visit HMMD, where they will be seen by an HIAE physician or nurse specialist via telemedicine equipment. This is an ongoing project supported by the HIAE and the Ministry of Health, with benefits reported among patients seen in the HMMD emergency room [19].Clinical management updating DLCA DLC based on the Brazilian ACSC criteria, focusing on physicians, nurses, and multi-professional staff, will be implemented. The DLC will be hosted by the HIAE Teaching Department’s structured platform, Taleo™. This knowledge platform was conceived to transmit and record web conferences, host discussion forums, and store and transfer archives. Other educational resources, such as structured clinical cases, will be developed to illustrate situations faced by health providers in real-world scenarios.The DLC will be divided into five modules, each 8 weeks in duration, covering the Brazilian ACSC list: respiratory, cardiovascular, diabetes, gastroenterology and mixed infectious diseases, and major health risk factors (smoking, alcoholism, drugs, pain, nutrition, and physical inactivity). Web conferences will be transmitted and recorded on a weekly basis. The 18 PCUs and HMMD will participate in the web conferences, which will feature a presentation on an ACSC by a professional expert speaker and a professional generalist’s comments on specific issues to provide participants with updated evidence-based knowledge. A tutor will encourage discussions in the forum, using a structured clinical case as a tool to demonstrate the applicability of the scientific evidence. The use of the ACSC-related guidelines and/or of evidence-based protocols will be emphasized. After each module, a face-to-face meeting will be carried out to emphasize teamwork and clinical decision-making processes, wrapping up the module content with mixed discussion groups tasked with generating proposals from the health providers for applying evidence-based recommendations at their care facilities. The DLC participants will be evaluated based on their participation in the discussion forums, weekly quizzes, and a final exam at the end of each module. Additionally, the participants will use a structured questionnaire to evaluate each module in terms of their satisfaction with the DLC structure, content, relevance to clinical practice, and feasibility of application in the workplace [see Additional file 1].

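### Objective 3 measures impact in all hospital admissions, with no restriction or contrast by primary care unit, although only 18 of the 31 referring units are linked to the platform and invited to the course

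*Protocol article*

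**What the plan says.** Table 1 of the protocol article (Research setting) states Objective 3 as "To verify the impact of the two strategies (communication and course) on patients’ hospital outcomes", namely 30-day readmission, length of stay and mortality. The participants cell for that objective reads "All hospital admissions of adult patients who had at least one ACSC from 2013 to 2017". It carries no condition on the patient's PCU. In the same row, Objective 4 is limited to patients registered at a PCU enrolled in the study.

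On the hospital's catchment, Research setting says "It is the unique referral hospital for 600,000 people who are registered in 31 PCUs covered by the primary care teams". On reach, Interventions says that the platform "allows the sharing of patients’ information, documents, and treatment plans between the hospital and 18 PCUs". The web conferences of the course are for those 18 PCUs and the hospital. The 18 share one managing organization and "will be selected as a convenience sample".

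The Objective 3 measures include "episodes in the emergency department, reference PCU", so the variable that separates linked from unlinked patients is recorded. The analysis cell gives "generalized estimating equations for length of stay, logistic models for mortality" and kernel density mapping, and names no comparison by PCU group. The section on the design of the impact evaluation names historical controls as the only comparator.

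**The concern.** An impact estimate needs a population that could have received the intervention, or a stated contrast between those who could and those who could not. Objective 3 as printed has neither. Thirteen PCUs get no admission alert and no discharge summary through the platform, and their staff are not on the course. Their patients nevertheless fall inside the population in which impact is to be shown.

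Two things follow if the objective is analysed as a before/after comparison over that population. First, the part of the effect that works through the PCUs is averaged with patients whom it cannot reach, so a null result could be dilution. Second, with historical controls only, anything that changed across the hospital between 2013 and 2017 is read as effect, so a positive result could be trend. The article describes one such change: a Lean Six Sigma project on record quality at the hospital and the PCUs, completed in March 2016 (Patients' medical records; Study status).

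**Working it through.** **The plan's own figure.** The stated sample size of 560 belongs to Objective 4. With 10 events per covariate (an assumption; the article gives only a citation), 10 × 9 / 0.16 = 562.5, so 560 reproduces. Objective 3 has no calculated size. It takes all eligible patients, with 3422 in 2013–2014.

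**Inputs from the article.** Baseline 30-day readmission 16%; 3422 patients in two years; 18 of 31 PCUs linked; significance level 5% (two-sided assumed).

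**Assumptions, because the article does not give them.** Share of admissions from the 18 PCUs, s = 18/31 = 0.58 (PCUs of equal size, and no patients from outside the 31); 3422 patients in each period; a 20% relative reduction in linked patients, 16.0% to 12.8%, or 3.2 points; no effect elsewhere. Clustering and repeat admissions are ignored.

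**Dilution.** Difference over all admissions = s × 3.2 = 0.581 × 3.2 = 1.86 points.

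**Power, two proportions.**
- All admissions, 3422 per period, 16.0% against 14.14%: 57.5%.
- Enrolled PCUs only, 0.581 × 3422 = 1987 per period, 16.0% against 12.8%: 82.0%.

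Under these assumptions, adding the other patients lowers power although the sample is larger.

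**Period-by-PCU-group contrast (difference-in-differences).** With 1987 linked and 1435 other patients per period, the variance is 0.16×0.84/1987 + 0.128×0.872/1987 + 2×0.16×0.84/1435 = 0.000311, so the standard error is 0.0176. Power = Φ(0.032/0.0176 − 1.96), about 44%.

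**Sensitivity.**

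| Setting | All admissions | Enrolled only | Contrast |
|---|---|---|---|
| s = 0.4 to 0.8, 20% reduction | 31% to 85% | 67% to 92% | 31% to 45% |
| s = 0.58, 15% reduction | 36% | 57% | 27% |
| s = 0.58, 25% reduction | 77% | 95% | 63% |

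**Spillover through ward staff.** If other patients receive a fraction c of the effect, the all-admissions difference is 0.581 × 3.2 + 0.419 × c × 3.2.
- c = 0.25: 1.86 + 0.34 = 2.19 points, power 72%. The contrast estimates 2.4 points, power 28%.
- c = 0.50: 1.86 + 0.67 = 2.53 points, power 84%. The contrast estimates 1.6 points, power 15%.

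**Detectable effect of the contrast at 80% power.** Assume 18 months before and 24 after at the stated volume, a split that the article does not give. Then n = 3422 × 18/24 = 2566 before and 3422 after, of which linked 1490 and 1987, other 1076 and 1435. SE = √(0.16×0.84 × (1/1490 + 1/1987 + 1/1076 + 1/1435)) = 0.0194, and 2.8 × 0.0194 = 5.4 points. The linked patients alone give 2.8 × √(0.16×0.84 × (1/1490 + 1/1987)) = 3.5 points.

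**The case against.** A reader might infer that the plan pools all 31 PCUs into one estimate and counts patients of the other 13 as exposed. The article says neither. The participants cell may describe data capture only, the analysis cell is a one-line list of models, and the article is a condensed text. What stands is narrower: the population is unrestricted and no exposure contrast is stated, while the neighbouring objective does carry the restriction.

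A reader might also infer that the other patients are untouched. That is not supported. Hospital staff take the course too: 43 + 73 + 29 + 12 = 157 of the 359 eligible providers are from the hospital's general clinic wards. The hospital serves all 31 PCUs, and length of stay and mortality are outcomes that ward staff can influence. All admissions is therefore a defensible secondary population, and dilution is less than 18/31 implies. With 50% spillover the power loss disappears (84% against 82%), although the estimate still falls short of the effect in linked patients (2.5 against 3.2 points).

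A claim that dilution triples the required sample (1/0.581² = 2.97) would mislead, because it compares with a fully exposed sample of equal size. Restriction also discards admissions. For 80% power, the base case needs 5819 admissions per period over all PCUs, or 1889 from enrolled PCUs, which means 1889/0.581 = 3253 admissions in total. The ratio is about 1.8.

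Finally, historical control is a declared choice, and the Discussion concedes limits in isolating the effects. The sized cohort and the models labelled for readmission belong to Objective 4, which is already restricted, so dilution does not reach that analysis.

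**Conclusion.** The point holds for Objective 3 as an unrestricted population with no stated exposure contrast. In the base case, a before/after comparison over all admissions shows 1.9 of 3.2 points with about 58% power, against 82% in enrolled PCUs. With 25% to 50% spillover it shows 2.2 to 2.5 points. These sizes rest on an assumed share of admissions from the 18 PCUs, an assumed effect and an assumed later volume. The direction of the bias needs only that unlinked patients benefit less than linked ones. Confounding with trend is separate and applies to any purely historical comparison here, including one restricted to the 18 PCUs.

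It is tempting to conclude that the contrast with the other 13 PCUs should be the main estimate. The documents do not support that. The 18 are a convenience sample under one manager, so the groups are not equivalent. Parallel trends would have to be assumed. The contrast also subtracts the hospital-staff part of the course, which is part of what Objective 3 sets out to measure. Its base-case power is 44%. It is a supporting analysis.

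**What to change.** - Classify every Objective 3 admission by reference PCU (18 enrolled or other) and by period, and state the date that divides the periods.
- Make the before/after comparison in the 18 enrolled PCUs the main analysis of the combined strategies.
- Keep the all-admissions comparison as secondary, because ward-staff training reaches all patients.
- Report beside these a period-by-PCU-group contrast with clustering by PCU, read as the PCU-linked increment beyond hospital-level exposure. State that it relies on parallel trends and a non-equivalent group.
- Report the observed share of admissions from the 18 PCUs, which replaces the 0.58 assumed here.

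The cost is one classification variable and one model term, with no new data collection. The downside is that the contrast is imprecise: about 5.4 points detectable with 80% power under the assumed volumes, against about 3.5 for the enrolled-PCU comparison. It should therefore be presented as support for the main estimate and not in its place.

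### The Objective 3 impact population covers all adult ACSC admissions, although only 18 of the hospital's 31 PCUs are linked to the platform, so a before-after estimate over it is biased toward no effect

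*Protocol article*

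**What the plan says.** All places are in the Methods/design part of the protocol article.

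- **Catchment (Research setting).** Of the hospital: "It is the unique referral hospital for 600,000 people who are registered in 31 PCUs covered by the primary care teams". The 18 PCUs run by one managing organisation "will be selected as a convenience sample".
- **Platform (Interventions).** It shares patient information, "documents, and treatment plans between the hospital and 18 PCUs". Table 1 (Objective 1, Procedures) describes an exchange in which the hospital alerts the PCU, the PCU manager replies, the reply enters the hospital record, and the discharge summary goes back to the PCU.
- **Course (Interventions).** It covers the same units and the hospital: "The 18 PCUs and HMMD will participate in the web conferences". The Health professionals section counts both PCU and hospital ward staff as eligible.
- **Objective 3 population (Table 1, Participants/Research units).** "All hospital admissions of adult patients who had at least one ACSC from 2013 to 2017". The sample size row takes all eligible patients and reports 3422 for 2013–2014.
- **Objective 4 population (same row, next cell).** Patients must be "registered at any PCU enrolled in the study".
- **Objective 3 measures (Table 1).** The patient variables include "readmissions, episodes in the emergency department, reference PCU".
- **Objective 3 analysis (Table 1).** Summary measures with confidence intervals, generalized estimating equations for length of stay, logistic models for mortality, and kernel density of addresses. No listed analysis uses the reference PCU.

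**The concern.** The platform needs a PCU at the other end. For a patient of one of the 13 unlinked PCUs there is no linked unit to answer the admission alert or receive the discharge alert, and the patient's primary care team is not among those offered the course. Such a patient can be affected only through hospital staff who took the course.

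The Objective 3 population nevertheless takes in these patients, and the aim attached to it is the impact of both strategies. The next cell of the same table restricts Objective 4 to enrolled PCUs, so the authors wrote the restriction where they wanted it. Followed as written, a comparison of earlier with later admissions mixes patients whose PCU was linked with patients whose PCU never was. A real benefit would look smaller than it is, and the result would not answer the question that Objective 3 asks.

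**Working it through.** **The plan's own figures.** Objective 3 states no effect size, power or exposed share, so there is nothing to reproduce for it. The only calculated sample size belongs to Objective 4. Assuming ten events per covariate, nine covariates and the stated 16% readmission, 10 × 9 / 0.16 = 562.5, which agrees with the stated 560. That cohort is already restricted to enrolled PCUs.

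**Inputs from the article**
- PCUs served 31; linked 18; not linked 31 − 18 = 13, and 13/31 = 41.9%.
- Eligible hospital staff 43 + 73 + 29 + 12 = 157; eligible PCU staff 85 + 85 + 12 + 20 = 202; total 359. Hospital staff are 157/359 = 44%.
- ACSC patients in 2013–2014: 3422. Readmission within 30 days: 16%.

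**Inputs not given, so assumed over a range**
- s, the share of ACSC admissions that come from the 18 PCUs.
- k, the fraction of the full effect that reaches other patients through hospital staff.

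**Attenuation.** If the full effect is D, the mean effect over all admissions is D × [s + (1 − s)k]. The fraction lost is 1 − s − (1 − s)k = (1 − s)(1 − k).

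| s | k | Attenuation |
|---|---|---|
| 18/31 = 0.581 | 0 | 41.9% |
| 0.581 | 0.25 | 31.5% |
| 0.581 | 0.50 | 21.0% |
| 0.581 | 0.75 | 10.5% |
| 0.40 | 0 | 60% |
| 0.80 | 0 | 20% |

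The value s = 18/31 assumes equal ACSC admissions per PCU. The attenuation is zero only if s = 1 or k = 1.

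**Illustration of power.** Assume a fall from 16% to 13% in fully exposed patients, 3422 patients in each period, s = 18/31 and a two-sided 5% test. Neither the effect nor the size of the later period is in the article.
- All admissions, k = 0: difference 3.0 × 0.581 = 1.74 points, later rate 14.3%, power 52%.
- All admissions, k = 0.5: difference 3.0 × (0.581 + 0.419 × 0.5) = 2.37 points, later rate 13.6%, power 79%.
- Restricted to the 18 PCUs: 3422 × 18/31 = about 1986 per period, difference 3.0 points, power 77%.

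Restriction gains power when spillover is absent and gains none at k = 0.5. The estimate over all admissions is too small in both cases.

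**The case against.** **Pooling is not stated outright.** The Objective 3 row can be read as a frame for data capture. Reference PCU is recorded and would allow restriction or stratification. The Patients text says that data on all eligible ACSC patients will be analysed, in a section that also requires registration in a selected PCU, so a restricted reading is possible. An analysis plan that is not shown may settle it. This stands in part: the article does not say that everyone is analysed as exposed. But the population for an impact objective is fixed in Table 1, fixed without the restriction, and set beside a cell that has it.

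**Patients of the other 13 PCUs are partly exposed.** Hospital ward staff are 44% of those eligible for the course and may treat any admitted patient. Length of stay and mortality could respond to that. This stands, and it is why k belongs in the calculation.

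**A reader might infer that the effect is diluted by roughly 40%.** The documents do not support that as a finding. It is a share of PCUs, not of admissions, and it becomes the dilution only with equal admissions per PCU and no spillover.

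**A reader might infer that the trial's main readmission analysis is compromised.** Objective 3 does name readmission as an outcome, but Table 1 places the main readmission analysis under Objective 4, which is already restricted.

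**Capturing all admissions has value.** In a design with historical controls, the 13 unlinked PCUs are the only concurrent comparison available. This stands and shapes the fix.

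**Conclusion.** The point holds as a mismatch between the Objective 3 aim and its stated population. A before-after estimate over all adult ACSC admissions is biased toward no effect by (1 − s)(1 − k). With s = 18/31 that is about 42% at k = 0, 21% at k = 0.5 and 10% at k = 0.75; with s from 0.4 to 0.8 and k = 0 it is 60% to 20%. These figures rest on assumed values of s and k, and no single one can be drawn from the article. A sure loss of power is not shown. The Discussion's general admission that the interventions' effects are hard to isolate does not deal with this, because the exposed group can be identified from a variable already collected.

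**What to change.** Keep capturing all adult ACSC admissions, but state two things for Objective 3.

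1. The impact estimate is defined on admissions whose reference PCU is one of the 18 participating units, in both the earlier and the later period.
2. Admissions from the other 13 PCUs serve as a concurrent comparison, through a period-by-PCU-group term in the models for readmission, length of stay and mortality.

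State how these are to be read. The restricted estimate removes the dilution but remains a before-after comparison. The interaction adjusts for trends common to both groups but estimates only the part of the effect that does not spill over, D(1 − k), so spillover through hospital staff makes it conservative.

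**Cost.** A change of wording in the analysis, since reference PCU is already on the list of variables. The restricted estimate uses fewer admissions (about 1986 of 3422 per period if s = 18/31). Some records will have a missing or outdated reference PCU, so a rule for assigning them is needed.
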